### 2.4. Eligibility Criteria: Inclusion Criteria

(1)Male and female participants aged 19–80 years.(2)Total Insomnia Severity Index (ISI) score ≥ 15.(3)Diagnosis of insomnia disorder according to DSM-5 criteria.(4)Voluntary participation and signing of an informed consent form after adequate explanation of the purpose and procedure of this clinical trial and any risks and potential for adverse effects from this trial procedure.

### 2.5. Eligibility Criteria: Exclusion Criteria

(1)Changes in the type or dosage of regularly used sleeping pills within the last 4 weeks(2)Korean medicine treatment (acupuncture, moxibustion, cupping, and herbal medicine) to improve insomnia within the last 4 weeks.(3)Initiation of health supplements or other non-pharmacological therapies (e.g., cognitive behavioral therapy and meditation) to improve insomnia within the last 4 weeks or plans to start the therapies during the clinical trial period.(4)Current participation in other clinical trials with interventions within the last 4 weeks(5)Shift workers.(6)Obvious pain that interferes with sleep or diseases causing insomnia.(7)Treatment for unstable (controllable) schizophrenia, bipolar disorder, and other mental disorders during the last 6 months or an anxiety or depression subscale score of ≥11 on the Hospital Anxiety and Depression Scale.(8)Current treatment for serious chronic diseases or terminal diseases (malignant tumor, tuberculosis, chronic liver disease, interstitial pneumonia, chronic renal disease, chronic heart disease, and other rare metabolic diseases).(9)Abnormal hormone levels on thyroid function tests (abnormal free T4 and thyroid stimulating hormone < 0.1 uIU/mL or >5.1 uIU/mL).(10)Clinically significant abnormalities in blood chemistry (aspartate aminotransferase and alanine aminotransferase > 2 times the upper limit; serum creatinine ≥ 1.5 times the normal upper limit).(11)Electrolyte abnormalities (5% more or less than the normal range).(12)Hypertension not controlled with antihypertensive drugs (systolic blood pressure >160 mmHg and diastolic blood pressure > 90 mmHg).(13)Diabetes mellitus not controlled with oral hypoglycemic agents or insulin-dependent diabetes (hemoglobin A1c level ≥ 7%).(14)Use of hemostatic agents (e.g., Greenmono, Advate, Monoclate-P, Facnyne, and BenFix) for cardiovascular diseases or hemostatic disorders.(15)Pregnancy, lactation, and disagreement with contraception methods (dual contraception, intrauterine contraceptive devices, and spermicides) during the clinical trial.(16)Difficulty with adherence to the study protocol.(17)Deemed unsuitable for participation by the investigator.

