### 2.2. Participants Recruitment and Study Schedule

A total of 138 participants with insomnia will be recruited and registered for competitive enrollment. Potential participants will be recruited through internal advertisements on bulletin boards and the homepages of each clinical institution, external advertisements in local newspapers, subway advertisements, and flyer advertisements. The investigators, who are qualified neuropsychiatrists of Korean medicine, will explain the purpose, treatments, procedures of the clinical trial, and any risks and potential for adverse effects that may occur during this trial procedure. Participants will be asked to sign informed consent forms after investigators sufficiently explain this clinical trial, and receive a copy of the consent form. The investigators will then diagnose the insomnia disorder according to DSM-5 criteria. Eligible participants will be randomly assigned to the pharmacopuncture or acupuncture group in a 2:1 ratio at visit 1. They will visit the research institution 12 times and undergo 10 treatments 5 times every 2 weeks for 4 weeks (visits 1–10). Within 1 week of treatment completion, a post-intervention assessment will be conducted (visit 11), and a follow-up assessment (visit 12) will be performed 4 weeks after treatment completion. The timeline of enrollment, treatment, and evaluation of the participants is summarized in Table 1, and a flowchart of the trial is presented in Figure 1. Additionally, 15 consecutive participants from each group enrolled at the Pusan National University Korean Medicine Hospital after random randomly assignment will undergo polysomnography, melatonin, and cortisol saliva studies on the day before the initiation of treatment (visit 1) and at the post-intervention evaluation (visit 11).

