### 2.7. Intervention

#### 2.7.1. Experiment Group: Pharmacopuncture

Since this trial is a pragmatic study that reflects Korean medical clinical practice, in which personalized treatment is provided according to the patient’s clinical status, the types and methods of pharmacopuncture, acupoints, amount of injection, and depth of injection have not been predetermined. Rather, the health practitioners (Korean medicine doctors) will determine the treatment procedure based on the participant’s clinical status. However, in this trial, the types of pharmacopuncture are limited to placental, Hwangryunhaedok-tang, and Bufonis venenum pharmacopuncture; these are already performed at each research institution and are the most commonly used insomnia treatments in a previous survey [36].

For pharmacopuncture, the acupoints GV20, Ex-HN3, Ex-HN22, GB12, HT7, CV4, and CV6, which were used for insomnia treatment in a previous study [41], will be used, but we will allow the Korean medical doctors to change the acupoints used according to their clinical decision based on the patient’s symptoms and condition.

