### 2.8. Concomitant Treatment

Medications that have been used 4 weeks prior to participation and medications used for other medical conditions (hypertension, diabetes mellitus, hyperlipidemia, and pain) will be allowed. The participants will be allowed to receive medical care for other conditions that do not affect the treatment results during the trial period. All details regarding concomitant treatment will be investigated at every visit and recorded in the medical records and CRFs.

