### 2.12. Criteria for Discontinuation and Withdrawal

Treatment will be discontinued and participation will be withdrawn according to the following criteria: (1) Request for discontinuation or withdrawal of consent by participants or their legal representative; (2) diagnosis of any medical condition that makes the participant ineligible for this trial; (3) incidence of any serious AEs; (4) violation of the study protocol; (5) changes in dosage or type of sleeping pills already used during the trial period (from screening test to post intervention); (6) loss to follow-up; (7) use of any medications or undergoing therapies that will affect the study results without the permission of investigators; (8) more than three consecutive absences from intervention or participation in less than seven sessions of the intervention; and (9) other conditions wherein participation is judged to be inappropriate by the investigator in charge.

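### Exclusion (14) appears to name the wrong drug class for cardiovascular disease, so with section 2.8 it lets in some anticoagulant or antiplatelet users

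*Protocol article*

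**What the plan says.** Section 2.5, exclusion (14), removes candidates for "Use of hemostatic agents (e.g., Greenmono, Advate, Monoclate-P, Facnyne, and BenFix) for cardiovascular diseases or hemostatic disorders". This is the only exclusion that concerns drugs acting on hemostasis.

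Section 2.8 sets the rule for other drugs: those "used 4 weeks prior to participation and medications used for other medical conditions (hypertension, diabetes mellitus, hyperlipidemia, and pain) will be allowed". It makes no exception for any drug class.

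Three other rules could reach a user of anticoagulant or antiplatelet drugs:

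- Exclusion (8): "Current treatment for serious chronic diseases or terminal diseases", with a list in brackets that includes chronic heart disease.
- Exclusion (17): "Deemed unsuitable for participation by the investigator".
- Section 2.12, ground (9), which lets the investigator withdraw a participant whose continued participation is judged inappropriate.

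On exposure, section 2.2 has participants "undergo 10 treatments 5 times every 2 weeks for 4 weeks". Section 2.7.1 says of pharmacopuncture that the "amount of injection, and depth of injection have not been predetermined". Section 2.7.2 likewise leaves insertion depth to the practitioner in the acupuncture arm.

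**The concern.** The mismatch lies inside one sentence. A drug that promotes hemostasis is a natural treatment for a hemostatic disorder. It is not what one expects a patient to take for cardiovascular disease, where the drugs relevant to injection and needling act in the opposite direction. Taken literally, the cardiovascular limb of (14) excludes almost no one.

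What is at stake is participant safety and a single eligibility rule applied alike at three sites. Candidates up to age 80 are eligible, and both arms involve repeated skin penetration at a depth the protocol does not fix. A site that follows the letter of (14) would enroll a stable anticoagulant user. A site that follows what it takes to be the intent would not. The 2:1 allocation was chosen partly to gather safety data on pharmacopuncture, so it should be clear who may be treated.

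**Working it through.** The protocol gives no figure on this point, so the check is to read the rules together.

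**1. What (14) reaches.** It reaches a user of hemostatic agents. It does not reach a user of anticoagulant or antiplatelet drugs, because those are not hemostatic agents. The product examples do not extend it. They appear to be clotting-factor products, which is general knowledge that the argument does not need.

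**2. What section 2.8 does with such a user.** Its first limb allows drugs already in use four weeks before participation, without restriction by class. Its second limb allows drugs for other conditions and lists four, none of them thrombotic. Even if that list is read as complete, the first limb is enough to permit a stable anticoagulant or antiplatelet drug.

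**3. Whether another exclusion closes the gap.**

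| Rule | Reaches an anticoagulant or antiplatelet user as such? |
|---|---|
| (8) serious chronic or terminal disease | In part: chronic heart disease is listed. Stroke, venous thrombosis, peripheral arterial disease and preventive aspirin are not |
| (9), (11), (13) thyroid, electrolyte and HbA1c limits | No |
| (10) "Clinically significant abnormalities in blood chemistry" | No: the limits given are for liver enzymes and creatinine, not clotting |
| (17) investigator judgment | Only by discretion |

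Table 1 schedules laboratory tests at screening without listing them. A clotting test may be among them, but no exclusion depends on one.

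**4. Whether a withdrawal ground in section 2.12 closes it.** Ground (7) covers "use of any medications or undergoing therapies that will affect the study results without the permission of investigators", which concerns interference with results and not bleeding. Ground (2) refers back to eligibility, so it adds nothing for a drug that eligibility does not mention. Ground (3) acts only after a serious adverse event. Ground (9) is discretion again.

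**5. Who is left.** Anticoagulant or antiplatelet users on stable treatment, outside (8), and not removed by discretion under (17) or ground (9).

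**6. Exposure of each such participant.** At most 10 sessions (section 2.2). The chance of the injection arm, from the planned group sizes in section 2.3, is 92/138 = 0.667. That ratio does not measure bleeding risk, since the other arm is needled too.

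**7. How many.** This cannot be derived. The document gives no rate of anticoagulant or antiplatelet use, and none is assumed here.

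**The case against.** The strongest reply has five parts.

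- **Intent is inferred.** If the listed products are clotting-factor products, class and examples agree, and only the words on cardiovascular disease are out of place. Nothing in the text shows that the authors set out to exclude anticoagulant or antiplatelet users. This stands. It is why the fix offers two routes, but on either route the sentence needs correcting.
- **The harm premise is external.** That these drugs raise bleeding risk with needling is general clinical knowledge. The protocol does not say so and gives no frequency. This stands too, and it limits the weight of the point.
- **Existing cover is substantial.** Exclusion (8) takes out a main group of likely users. Medical history, laboratory tests and an electrocardiogram are scheduled at screening or by the first visit. Concomitant treatment and adverse events are checked at every visit. Undetermined depth also lets a trained practitioner treat more cautiously. All of this is true, but none of it is a rule about these drugs.
- **A pragmatic trial may leave such patients to clinical judgment.** It may, but as a stated choice. At present the text appears to exclude someone on a cardiovascular ground and does not.
- **Only an article is visible.** Bleeding precautions may sit in the full protocol or the operating-procedure training. That answers a complaint about missing detail. Here the complaint is about what a printed criterion says, in a list detailed enough to give laboratory limits and brand names.

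A reader might go further and infer that the trial knowingly enrolls patients at high bleeding risk, or that many are affected. The document supports neither inference: it shows no such intent and gives no count.

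**Conclusion.** The point holds as a minor participant-safety correction. Exclusion (14) appears to name the wrong drug class for one of its two indications. Read with section 2.8, it admits some anticoagulant or antiplatelet users whose exclusion then depends on the investigator. The frequency is unknown and the per-participant exposure is at most 10 sessions.

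The conclusion rests on the literal wording of the article, and on the general clinical premise that these drugs matter when needling.

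Two further inferences should be resisted. The first is that the treatment comparison is biased. Eligibility is settled before allocation and the same criteria apply to both arms, so sample size, alpha and the primary comparison are unaffected. The second is that participants already enrolled on these drugs should leave the full analysis set, because section 2.13 removes those who did not meet the eligibility criteria. Someone who met version 1.1 as written when enrolled did meet them, and a later rewording does not change that.

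**What to change.** Reword exclusion (14) so that each class matches its indication:

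- (a) use of anticoagulant or antiplatelet drugs for cardiovascular disease;
- (b) a hemostatic disorder, or use of hemostatic agents for it, keeping the present product examples here.

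Add to section 2.8, after the allowed medications: *except drugs excluded under (14)*. This is a clarification, since an allowance for concomitant drugs should not override an exclusion. Apply both changes to new enrollment only.

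If the sponsor does mean to admit anticoagulant and antiplatelet users, the lighter route is to delete the cardiovascular limb of (14) and state needling and injection precautions for them.

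The cost is one amendment at three review boards while recruitment is under way. The first route also loses a few candidates and slightly narrows the population to which a pragmatic result applies. If the full version 1.1 already words (14) correctly, a correction to the article is enough.

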### 2.6. Randomization, Allocation Concealment, and Blinding

A statistical expert not involved in the assessment and intervention will generate the allocation sequence using a stratified block randomization method with the research institution as a stratification factor using the statistical program SAS 9.4 (SAS Institute, Cary, NC, USA). The randomization list will be delivered to each institution and stored in sealed opaque envelopes in a double-locked cabinet. The investigator will open the envelope to randomly assign the participants to the pharmacopuncture or acupuncture groups. The investigator will store the open envelopes in a double-locked cabinet and record the randomized number assigned to each patient on the electronic medical chart.

Due to the nature of the interventions, it will be impossible to achieve blinding of participants or health practitioners. Outcome measures will be assessed prior to treatment in separate rooms by assessors who are not involved in allocation and interventions to ensure assessor blinding. The assessors participating in this study are residents at the Department of Neuropsychiatry of Korean Medicine and clinical research coordinators who have completed research ethics education and standard operating procedure training related to this trial before trial initiation.

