## 2. Materials and Methods

### 2.1. Study Design

This multi-site, pragmatic RCT was conducted at Pusan National University Korean Medicine Hospital, Dong-eui University Korean Medicine Hospital, and Semyung University Korean Medicine Hospital in Chungju. The study protocol was approved by each research institution’s institutional review board (IRB) before trial initiation (Pusan National University Korean Medicine Hospital, Institutional Review Board: PNUKHIRB-2021004; Semyung University Korean Medicine Hospital in Chungju, Institutional Review Board: SMCJH 2110-12; and Dong-eui University Korean Medicine Hospital, Institutional Review Board: DH-2021-13). The IRB will approve any changes to the study protocol, including recruitment advertisements, informed consent forms, and case report forms (CRF). The study protocol was registered with the Clinical Research Information Service (CRIS) (no. KCT0006803).

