### 2.3. Sample Size

In this trial, the ratio of the pharmacopuncture group to the acupuncture group will be 2:1 in order to obtain data on the side effects (safety) of the pharmacopuncture while securing statistical power [38,39]. The sample size of this study was determined based on the study by Xian et al. [40]. The mean differences in PSQI scores before and after treatment in the experimental and control groups were estimated to be 6.9 (standard deviation = 2.51) and 4.93 (standard deviation = 2.70), respectively. Based on this, the effect size calculated using G Power software, version 3.1.9.4 (Franz Faul, Christian-Albrechts-Universittt Kiel, Kiel, Germany) was 0.92. The number of participants required is then 74 for the experimental group and 37 for the control group, given a 2:1 allocation ratio, two-sided significance level of 0.05, and 95% statistical power. Considering a dropout rate of 20%, the total sample size of the experimental and control groups will be 92 and 46, respectively.

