### 2.13. Statistical Analysis

Continuous variables will be presented as means and standard deviations, while categorical variables will be presented as frequencies (%) and percentiles. The homogeneity of the demographic characteristics and baseline variables between the two groups will be evaluated to choose the appropriate analysis methods. The independent t-test or Mann–Whitney U-test will be used for analysis, depending on the normality of data distribution. If there were significant between-group differences in baseline variables or demographic characteristics, regression analysis with covariates (analysis of covariance) will be conducted. The primary and secondary outcome measures will be analyzed in the same manner. We will also examine the consistency between objective and subjective sleep-related data obtained from actigraphy and patient-reported questionnaires.

Additionally, we will analyze the changes in sleep parameters assessed using polysomnography and sleep-related hormones before and after treatment in participants who underwent polysomnography. Both the full analysis set (FAS) and per-protocol analyses will be conducted. The FAS is the primary analysis of effectiveness and safety. It will include all participants initially assigned to each group, except those who did not meet the eligibility criteria, those who had not received any intervention, or those who had not completed any outcome measurements. The per-protocol analysis will include participants who have completed more than seven sessions. All statistical analyses will be performed by an independent statistical expert blinded to the allocation and procedure using SPSS version 25 (IBM, Chicago, IL, USA). Statistical significance is set at *p* < 0.05.

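### Randomisation is stratified by research institution, but the stated tests leave institution out; if institution predicts outcome, the analysis is conservative, with little power lost at the planned difference

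*Protocol article*

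**What the plan says.** Section 2.6 generates the allocation sequence "using a stratified block randomization method with the research institution as a stratification factor". No other stratification factor is named. Section 2.1 lists the sites: "Pusan National University Korean Medicine Hospital, Dong-eui University Korean Medicine Hospital, and Semyung University Korean Medicine Hospital in Chungju".

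Section 2.13 fixes the between-group analysis: "The independent t-test or Mann–Whitney U-test will be used for analysis, depending on the normality of data distribution". The one route to adjustment is conditional: "If there were significant between-group differences in baseline variables or demographic characteristics, regression analysis with covariates (analysis of covariance) will be conducted". The rule covers every efficacy endpoint: "The primary and secondary outcome measures will be analyzed in the same manner". Institution is not mentioned in Section 2.13.

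**The concern.** Blocking within hospital holds the arms close to 2:1 at each site, so differences between hospitals largely cancel out of the treatment contrast. A two-sample test that ignores site still counts those differences as error. The estimate is then more precise than its reported standard error says.

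The conditional ANCOVA would not be expected to repair this. It responds to imbalance between arms, and institution is the one variable the design deliberately balances. If another variable triggered the ANCOVA, nothing in Section 2.13 says that institution would join the model.

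A site effect on outcome is plausible. Sections 2.7.1 and 2.7.2 leave acupoints, technique and depth to the practitioner in both arms, and the primary outcome is a self-report from unblinded participants. At stake is efficiency, and the agreement of confidence intervals and p-values with the design. The treatment estimate is not biased.

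**Working it through.** **Inputs from the article.** Section 2.3 gives mean PSQI changes of "6.9 (standard deviation = 2.51) and 4.93 (standard deviation = 2.70), respectively", 74 and 37 evaluable participants, and "two-sided significance level of 0.05, and 95% statistical power". Section 2.1 gives three sites.

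**Assumptions, not in the article.** The share *s* of outcome variance due to institution runs from 0 to 30%. Sites are near-equal in size, with 2:1 balance inside each. The smaller true difference of 1.3 is also assumed.

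**Step 1: the plan's sample size.**
- Difference: 6.9 − 4.93 = 1.97.
- Pooled SD: √[(2.51² + 2.70²)/2] = 2.607.
- Standardised effect: 1.97/2.607 = 0.756.
- For 95% power at 2:1, a t-test needs 70 + 35. The Mann–Whitney version (normal data, relative efficiency 3/π) needs 74 + 37, with power 95.3%, which is the stated size.
- The printed effect size ("Christian-Albrechts-Universittt Kiel, Kiel, Germany) was 0.92") does not follow from these means and SDs. That is a separate matter; the working below uses 1.97 and 2.607.

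**Step 2: standard errors.**
- Unadjusted: SE = 2.607 × √(1/74 + 1/37) = 2.607 × 0.2013 = 0.525, whatever the value of *s*.
- True SE under balance within site: 0.525 × √(1 − *s*).
- Overstatement factor: 1/√(1 − *s*).

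**Step 3: type I error.** The t-test rejects when the estimate exceeds 1.982 × 0.525. In units of the true SE the cut-off is 1.982/√(1 − *s*). At *s* = 10% this is 1.982/0.949 = 2.089, a two-sided tail of about 3.9%.

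| Site share *s* | True SE | Unadjusted SE too large by | Type I error by formula | Type I error by simulation |
|---|---|---|---|---|
| 0% | 0.525 | 0% | 5.0% | 4.9% |
| 5% | 0.512 | 2.6% | 4.4% | 4.2–4.7% |
| 10% | 0.498 | 5.4% | 3.9% | 3.6–4.0% |
| 20% | 0.469 | 11.8% | 2.9% | 2.8–2.9% |
| 30% | 0.439 | 19.5% | 2.0% | 1.9% |

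The ranges span repeated simulations; the 0% and 30% rows come from one set. With institution in the model, type I error stays near 5% (4.7–5.1%) throughout.

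**Step 4: power.** Results are from 20,000 simulated trials per setting with 74 v 37 evaluable, unadjusted v institution-adjusted.

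| Site share *s* | True difference 1.97 (planned) | True difference 1.3 (assumed) |
|---|---|---|
| 0% | 96.1 v 96.1 | 68.9 v 69.0 |
| 5% | 96.4 v 96.8 | 69.4 v 71.0 |
| 10% | 96.7 v 97.5 | 69.8 v 73.7 |
| 20% | 97.5 v 98.6 | 71.0 v 78.4 |
| 30% | 98.3 v 99.4 | 71.9 v 83.5 |

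At 1.97 the loss for shares of 5–20% is 0.4 to 1.1 points here; a further simulation put it at up to 1.3. At 1.3 it is about 2 to 8 points over the same shares, and about 12 points at 30%.

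**The case against.** **No site effect is documented.** The article gives no between-hospital variance, and several features would limit it. Pharmacopuncture is restricted to three types already in use at each institution, default acupoints are set within each arm, practitioners complete common training, and the outcome is a change from baseline. This stands. The result is conditional on institution predicting outcome, and a reader should not infer that every confidence interval in the trial will be too wide.

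**The loss at the planned effect is trivial.** This also stands for the primary outcome if the true difference is 1.97: both analyses exceed the 95% target. The article does not support a claim that the trial is underpowered for this reason. The secondary outcomes, however, use the same tests and have no stated power calculation, so that margin cannot be assumed for them.

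**The error is in the safe direction.** Correct. A reader might infer from the mismatch of design and analysis that false positives are inflated. The reverse holds.

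**Stratification does not rule out imbalance.** Also correct. The full analysis set drops ineligible, untreated and unmeasured participants, and 20% dropout is allowed for, so sites could drift from 2:1. Institution is unlikely to reach the ANCOVA by the stated trigger, but this is not impossible.

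**Practitioner choice may produce interaction.** If treatment effects differ by hospital, a site main effect does not remove that. Practitioners choose technique in both arms, so a main effect remains plausible, but the figures above describe only that.

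**A covariate list belongs in the SAP.** This would answer silence. Section 2.13 is not silent: it names an unadjusted test and a specific rule for adjustment, and following it as written omits the stratification factor.

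**Only the t-test was calculated.** True. The same reasoning applies in direction to the unstratified Mann–Whitney test, but its size was not computed.

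**Conclusion.** The point holds as a conditional matter of efficiency. The stated analysis does not reflect the stated randomisation, and the adjustment rule is unlikely to correct this. If institution explains 5–20% of outcome variance, the unadjusted standard error is about 3–12% too large and the type I error falls from 5% to roughly 4.2–4.7% at the low end and 2.8–2.9% at the high end. With no institution effect the two analyses agree.

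For the primary outcome at the planned difference the practical cost is about 1 point of power. It matters more if the true effect is smaller than planned. The direction is firm; the size rests wholly on the assumed site share and, for the larger losses, on the assumed difference of 1.3. The trial remains valid without the change, which is worth making because it is almost free.

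**What to change.** State in Section 2.13, and in the SAP, that research institution enters the primary between-group model and the between-group models for secondary outcomes as a prespecified three-level fixed effect. Its inclusion should not depend on any baseline test. Where a rank analysis is reported, replace the unstratified Mann–Whitney test with a site-stratified (van Elteren) test.

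The cost is two degrees of freedom and a change of wording. No extra participants, visits or data are needed, and power is essentially unchanged if institution has no effect (96.1% either way at the planned difference).
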